### Participants

Full details of inclusion and exclusion criteria are presented in Table 3. Male and female participants aged 18–50 years are eligible for the study if they have PAH as defined by National Institute of Care and Health Excellence,^51^ including idiopathic PAH, heritable PAH, drug/toxin‐induced PAH, or PAH associated with connective tissue disease. Subjects are required to have symptomatic PAH with a reduced exercise capacity related to PAH (NYHA/WHO functional class II/III; 6MWD ≥150 m and <550 m) and a REVEAL 2.0 score of 6–10. An RHC within the 36 months before study enrollment to confirm precapillary disease, with a resting mPAP ≥25 mmHg and resting mean PVR ≥5 Wood units with precapillary wedge pressure (PCWP) ≤ 15 mmHg. PAH therapy at stable doses of standard of care treatments for at least 90 days before screening is also required. Subjects with pulmonary hypertension category 2–5 and those likely to undergo lung transplantation within the next 6 months are excluded from the study. Participants are also ineligible to take part in the study if the CardioMEMS PA Sensor cannot be implanted due to active infection, recurrent thrombosis, intolerance of RHC, PA branch diameter <7 mm in the target implant vessel, or unable to take dual antiplatelet/anticoagulant therapy for 1 month after CardioMEMS PA Sensor implantation.

**Table 3 pul212323-tbl-0003:** Inclusion and exclusion criteria.

Inclusion criteria
1. Willing and able to sign a written informed consent before any study‐related procedures and able to understand and follow instructions; return to the study unit for specified study visits; and able to participate in the study for the entire period. 2. Male or females aged 18–80 years. 3. BMI of 18–40 kg/m^2^ at screening; if BMI is >35 kg/m^2^, subject chest circumference should be <65 inches (165 cm). 4. Subjects with PAH belonging to one of the following subgroups of NICE Clinical Classification of PAH category: a. Idiopathic PAH b. Heritable PAH c. Drug or toxin‐induced (anorexigen or methamphetamine use) d. PAH associated with connective tissue disease 5. Subjects with PAH who are symptomatic and have reduced exercise capacity due primarily to their PAH diagnosis, having been assessed by qualified individual, that is, physician, physician assistant, or nurse practitioner to be in NYHA/WHO functional class II or III and having a REVEAL 2.0 score of 6–10. 6. PAH therapy at stable doses of standard‐of‐care therapies for at least 90 days before screening. 7. Subject has most recent (within the last 36 months) hemodynamic assessment of PAH by RHC demonstrating a persistent resting mPAP ≥25 mmHg and resting mean pulmonary vascular resistance (PVR) ≥5 Wood Units with pulmonary capillary wedge pressure ≤15 mmHg. 8. Subject is willing to undergo CardioMEMS PA Sensor implantation and RHC before randomization or has had the CardioMEMS PA Sensor implanted previously. 9. 6MWD ≥150 and <550 m at screening 10. Female subjects of childbearing potential must be willing and able to practice effective contraception during the study and continuing contraception for 30 days after their last dose of study drug. Female subjects of non‐childbearing potential are defined as being surgically sterilized by bilateral tubal ligation, bilateral oophorectomy, or hysterectomy. A female subject 45–60 years of age, who is post‐menopausal for at least 1 year, and has a follicle‐stimulating hormone level confirmation indicating post‐menopausal status will be considered of non‐childbearing potential. Female subjects >60 years of age are considered post‐menopausal and of non‐childbearing potential.
Exclusion criteria 1. Pulmonary hypertension category 2–5. 2. Adult congenital heart disease (ACHD). 3. Concomitant medical or psychiatric disorder, condition, history, or any other condition that in the opinion of the Investigator would either put the subject at risk or impair the subject's ability to participate in or complete the requirements of the study or confound the objectives of the study. 4. A concomitant medical disorder that is expected to limit the subject's life‐expectancy to ≤1 year. 5. REVEAL 2.0 score of ≤5 or ≥11. 6. Heart failure with preserved ejection fraction defined as >50% ejection fraction (with signs and symptoms of heart failure) or left atrial volume >34 mL/m^2^. 7. Subject is not able to have CardioMEMS HF System implanted due to: a. An active, ongoing infection defined as being febrile, an elevated white blood cell count, on intravenous antibiotics, and/or positive cultures (blood, sputum, or urine). b. History of current or recurrent (≥2 episodes within 5 years before consent) pulmonary emboli and/or deep vein thromboses. c. Cannot tolerate RHC. d. PA branch inner diameter <7 mm in a descending branch within the left or right lower lung lobe (target implant vessel). e. Unable to take dual antiplatelet or anticoagulation therapy for 1 month after CardioMEMS implantation. 8. Likely to undergo lung transplantation within the next 6 months. 9. Untreated, moderate to severe obstructive sleep apnea. 10. Evidence of significant chronic thromboembolic disorder as determined by the Investigator or recent pulmonary embolism within 6 months before screening. 11. Uncontrolled hypertension (˃160/100 mmHg, confirmed by duplicate seated readings) at two or more historical visits within 3 months before screening. 12. Sustained systolic blood pressure <95 mmHg and/or diastolic blood pressure <50 mmHg (confirmed by duplicate seated readings) on at least three consecutive occasions (self‐monitored or office) before or at screening, or overt symptomatic hypotension. 13. Sustained resting heart rate >120 beats per minute (confirmed by duplicate assessments of office vital signs) or consecutive ECG assessments on at least three consecutive occasions before or at screening. 14. A history of a bleeding disorder. 15. Thrombocytopenia (platelets <150,000/mm^3^). 16. Known porphyria, mitochondrial disease, or urea cycle disease. 17. A history of chronic pancreatic disease. 18. Pregnant or lactating. 19. A positive result from serology testing at screening for HIV, HBsAg, HCV; but if the subject has a historical diagnosis (before screening) of being positive for HIV, HBsAg, or HCV must be clinically stable and if on therapy, be on stable therapy for ≥3 months before screening. A subject should not have active COVID‐19; however, those with previous COVID‐19 are permitted. 20. Participation in another investigational drug study within 30 days before screening or participating in a non‐medication study which, in the opinion of the Investigator, would interfere with the study compliance or outcome assessments. 21. Subject is on regular treatment with VPA, other antiseizure medications, or other prohibited medications that cannot be discontinued at the screening visit. 22. Regular anticoagulation or DAPT that cannot be discontinued at the screening visit; however, during the baseline period following CardioMEMS implantation, DAPT is allowed according to clinical practice for up to 4 weeks. 23. More than mild mitral or aortic valve disease, LVEF <50%, or left ventricular regional wall motion abnormality suggestive of active coronary artery disease on two‐dimensional‐echocardiogram at screening. 24. Subject has a forced expiratory volume in 1 s (FEV1)/forced vital capacity <70% (absolute), FEV1 ≤50% or total lung capacity (TLC) <70% predicted on pulmonary function testing (PFT); for potential subjects with TLC 60%–69% predicted, non‐contrasted computerized tomography (CT) scan must be performed to exclude subjects with more than mild interstitial lung disease. PFTs should have been obtained within 3 years before screening. 25. Clinically significant renal dysfunction (eGFR of <30 mL/min/1.73 m^2^) as calculated by Modification of Diet in Renal Disease (MDRD) at screening. 26. Significant liver dysfunction as measured by any one of the following at screening (including subjects with acute or chronic hepatitis as well as subjects with own or family history of serious hepatitis, especially drug related): a. ALT >2.0 × ULN. b. AST >2.0 × ULN. c. Serum bilirubin ≥1.6 mg/dL or >2.0 × ULN. 27. A known history of substance abuse including alcohol abuse within the 1 year before screening that in the opinion of the Investigator would impair the subject's ability to participate in or complete the requirements of the study. 28. Any major surgical procedure or trauma within 30 days before screening or planned surgical procedure during the study period. 29. Any inpatient hospitalization (defined as >23 h) within 30 days before screening. 30. Enrollment within 90 days before screening or plans to enroll during the study into a cardiopulmonary rehabilitation program. 31. Known hypersensitivity to study drug or any of the excipients of the drug formulation.

Abbreviations: 6MWD, 6‐minute walk distance; ALT, alanine aminotransferase; AST, aspartate aminotransferase; BMI, body mass index; DAPT, dual antiplatelet therapy; eGFR, estimated glomerular filtration rate; HBsAg, hepatitis B surface antigen; HCV, hepatitis C; HIV, human immunodeficiency virus; LVEF, left ventricular ejection fraction; mPAP, mean pulmonary artery pressure; NICE, National Institute of Health and Care Excellence; NYHA, New York Heart Association; PA, pulmonary artery; PAH, pulmonary arterial hypertension; PVR, pulmonary vascular resistance; RHC, right heart catheterization; ULN, upper limit of normal; VPA, valproic acid; WHO, World Health Organization.

### Sample size calculation

The main purpose of the study is to evaluate safety/tolerability of three different doses of CS1. In addition, exploratory evaluations of many relevant measurements for patients with PAH (see previous text sections) will be performed. For sample size calculation for the study, the estimate was based on the potential effect of CS1 on mPAP, with analysis according to multiple readings that increase the precision of PA pressure determination. A sample size of 10 subjects per dose level group has an 80% power to detect a difference in means of 15%, assuming that the common standard deviation is 5, with a 5% significance level.

PA pressure (mPAP) AUC will be the first secondary endpoint that will be tested statistically since the power of the study is based on that variable.

### Statistical analysis

The study protocol and Statistical Analysis Plan will be published as appendices to the primary publication following the end of the study.

The Safety Analysis Set includes all randomly assigned participants who receive at least one dose of study drug and participants will be analyzed as treated. The PK Analysis Set will include all participants in the Safety Analysis Set who have at least one evaluable post‐baseline PK sample, and this will be used for all PK analyses.

All data listings, summaries, figures, and statistical analyses will be generated using SAS version 9.4. Summaries will be presented by dosing cohort and overall. The exploratory efficacy endpoints will summarized descriptively and analyzed using both intention to treat as well as per protocol approaches. Of the exploratory efficacy endpoints, mPAP which the study is powered for, will be tested first to detect mean differences among dosing groups. Descriptive statistics for categorical variables will include the number and percentage of participants with each characteristic. Percentages will be based on the number of participants with non‐missing values. Descriptive statistics for ordinal and continuous variables will include the number of participants, mean, median, standard deviation, minimum value, maximum value.

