**Figure 3 pul212323-fig-0003:**
[figure not shown]
Study design schematic. C, clinic visit; ET, early termination; TC, telephone or video call; V, visit.

Following screening, subjects undergo RHC with classical measurements and have a CardioMEMS PA Sensor implanted according to published methods,^24^, ^26^ followed by the baseline period for subjects to become familiar with the system, its measurements, how to send the data collected, and to establish a true ambulatory baseline PA pressure profile. During the study, mean PA pressure (mPAP) and other hemodynamic parameters from the CardioMEMS PA Sensor are measured and data captured once daily in the morning while the participant is in the supine position. Data are transferred electronically to a secured web‐based data repository.

The study is conducted in accordance with the ethical principles of the Declaration of Helsinki and International Conference on Harmonization Good Clinical Practice guidelines. The study protocol (version 3.0; December 9, 2022) was approved by the ethics committees at all participating study sites. CardioMEMS HF was approved for all forms of heart failure by the United States Food and Drug Administration (FDA) in 2014.^48^

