### Outcome measures

The primary objective of the study is to evaluate the safety and tolerability of three doses of CS1, with secondary objectives of exploratory efficacy, measures of PAH progression and PK of CS1. For a full description of the primary and secondary outcomes see Tables 1 and 2.

**Table 1 pul212323-tbl-0001:** CS1 Phase 2 study endpoints and outcome measures.

*Primary endpoint*	
Safety outcomes	Adverse events Adverse events of special interest Serious adverse events Adverse device events related to the CardioMEMS HF System, including adverse device events, serious adverse device events, and unanticipated adverse device events Laboratory parameter abnormalities Change in vital signs Bleedings Change in ECG parameters
*Exploratory endpoints*	
Change from baseline to the end of treatment in right heart catheterization parameters—comparison between CS1 doses	PVR, PVRI, SVR, SVRI, PVRI:SVRI ratio, cardiac output and index, SV, SVI, RAP, right ventricular end diastolic pressure, PA systolic, diastolic and mean pressure, PCWP, RAP/PCWP, pulmonary compliance, pulmonary elastance, cardiac efficiency, cardiac power
REVEAL 2.0—comparison between CS1 doses	Score, strata, mean, and number of participants with reduction in score of ≥1 point at each visit, percentage of participants with change to low‐risk status (score <6), percentage of participants with change to ultra‐low‐risk status (score <5), percentage of participants with change to and maintenance of high‐risk status, percentage of participants with change to and maintenance of intermediate risk status
REVEAL Lite 2—comparison between CS1 doses	Score, strata, mean, and number of participants with reduction in score of ≥1 point at each visit, percentage of participants with change to REVEAL Lite 2 score <5, percentage of participants with change to REVEAL Lite 2 score <4, percentage of participants with change to and maintenance of high‐risk status, percentage of participants with change to and maintenance of intermediate risk status
Change from baseline to the end of treatment in patient‐reported outcomes—comparison between CS1 doses	Pulmonary Arterial Hypertension‐Symptoms and Impact Questionnaire Minnesota Living with Heart Failure® Questionnaire

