Change from baseline to the end of treatment in CardioMEMS PA Sensor measurements—comparison between CS1 doses	PA systolic, diastolic, and mean pressure, TPR, SV, SVI, pulmonary compliance, pulmonary elastance, cardiac efficiency, cardiac power, cardiac output and index, RVSW, RVSWI, RV efficiency (SV/mPAP)
Change from baseline to the end of treatment in cardiac MRI parameters—comparison between CS1 doses	PA sizes, right atrial area, RVEF, LVEF, SV, SVI, RV end diastolic and end systolic volume index, LV end diastolic and end systolic volume index, RV end diastolic volume:LV end diastolic volume ratio, pericardial effusion, RV end diastolic area, RV end systolic area, RV mass/index, PA relative area change, repetition time (TR; mild/moderate/severe), RV/PA coupling in relation to CardioMEMS
Change from baseline to the end of treatment in echocardiogram parameters—comparison between CS1 doses	RV end diastolic dimension, RV end systolic area, RV fractional area change, TAPSE, right atrial area, RV global, basal strain (TDIs’), systolic PAP, TAPSE/systolic PAP, RV global strain/systolic PAP, pericardial effusion, RV velocity time integral, PA acceleration time, TR (mild/moderate/severe)

Abbreviations: LV, left ventricle; LVEF, left ventricle ejection fraction; MRI, magnetic resonance imaging; PA, pulmonary artery; PAP, pulmonary artery pressure; RV, right ventricle; RVEF, right ventricle ejection fraction; RVSW, right ventricle stroke work; SV, stroke volume; SVI, stroke volume index; TAPSE, tricuspid annular plane systolic excursion; TPR, total pulmonary resistance; TR, repetition time.

The primary endpoint of the study includes AEs, AEs of special interest (liver toxicity, abnormal bleeding, anemia, thrombocytopenia, pancreatitis, tinnitus, dizziness, depression, and suicidal thoughts), serious AEs, adverse device effects related to the CardioMEMS HF System (adverse device effects, serious adverse device effects, and unanticipated adverse device effects, including those resulting from insufficient or inadequate instructions for use, deployment, implantation, installation, or operation, or any malfunction), laboratory parameter abnormalities, changes in vital signs, bleeding events and changes in ECG parameters (Table 1).

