Understanding hemodynamics at baseline and changes over time is also crucial to guide clinical management of patients with PAH. Notably, the recent Phase 2 clinical trial of sotatercept in PAH employed PVR as its primary endpoint, which was significantly different when comparing active treatment to placebo.^49^ It has been shown that the CardioMEMS HF System permits timely and consistent PA pressure monitoring that is associated with a more frequent medication changes and reduced hospitalizations in patients with heart failure regardless of left ventricular ejection fraction.^26^, ^31^, ^32^, ^34^, ^63^, ^64^, ^65^ Ambulatory PA pressure monitoring using CardioMEMS provides very frequent hemodynamic assessment in the patients’ normal environment, which more accurately assesses medication impact over time. Intermittent RHCs provide limited “real‐time” information about medication changes given the time between tests. This approach allows medication intervention studies to provide clearer data with fewer participants enrolled. Its use in the current study will provide greater insight into the real‐time evolution and stability/consistency of effects of CS1 at the level of pulmonary hemodynamics, PA and RV interactions, as well as provide important safety data using CardioMEMS in patients with PAH.

It is well‐established that the use of cardiac MRI is a valuable predictive tool for clinical worsening and mortality in PAH, in terms of tracking deterioration in RV function.^66^, ^67^, ^68^ In this study, the extensive imaging data captured will allow a precise insight into the adaptive change in RV response to therapy, which has been shown previously in a study of macitentan.^69^

In conclusion, CS1 represents a potential novel disease‐modifying treatment for PAH. The Phase 2 study described here will provide vital information regarding the safety of CS1 at three dose levels but will also include a broad range of endpoints encompassing clinical, hemodynamic, and PK parameters as well as patient‐reported outcomes. Topline results from this study are expected in the first quarter of 2024 and a quality analysis will be reported in the fall of 2023.

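### Implantation events belong to the primary safety endpoint, but the only stated safety population omits participants who were implanted and never dosed

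*Protocol article*

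**What the plan says.** **Endpoint.** Table 1 of the Protocol article lists under the primary endpoint "Adverse device events related to the CardioMEMS HF System, including adverse device events, serious adverse device events, and unanticipated adverse device events". The text under Outcome measures widens this to effects of the procedure itself, "including those resulting from insufficient or inadequate instructions for use, deployment, implantation, installation, or operation, or any malfunction".

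**Timing.** Under Study design: "Following screening, subjects undergo RHC with classical measurements and have a CardioMEMS PA Sensor implanted". A baseline period of up to 6 weeks follows, and randomization comes after it. Inclusion criterion 8 (Table 3) also places implantation before randomization, and it admits a participant who "or has had the CardioMEMS PA Sensor implanted previously".

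**Populations.** Under Statistical analysis: "The Safety Analysis Set includes all randomly assigned participants who receive at least one dose of study drug", analysed as treated. The PK set lies inside that set. Intention-to-treat and per-protocol approaches are named only for the exploratory efficacy endpoints. Summaries are planned by dose cohort and also overall.

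**Aim.** The Discussion expects the study to "provide important safety data using CardioMEMS in patients with PAH".

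**The concern.** Exposure to the implantation procedure begins weeks before anyone can qualify for the Safety Analysis Set. A serious complication, or a failed implant, is itself a reason for a participant not to reach randomization. Exclusion criterion 7 works in the same direction: it removes people who cannot tolerate catheterization or whose target vessel is too small, and either may come to light during the procedure. The participants most informative about procedural risk are therefore the ones most likely to be missing from the set.

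At stake is one component of the primary endpoint and a stated secondary use of the trial. The introductory sections say that only one CardioMEMS study in PAH has been published, with 26 patients. Any rate reported here would be read as a substantial part of the evidence, so its denominator should match the exposure.

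**Working it through.** **1. Who can be counted**

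| Participant | Exposed to in-study implantation | In the stated Safety Analysis Set |
|---|---|---|
| Implanted in study, randomized, dosed | yes | yes, including events before the first dose |
| Implantation attempted or completed, never randomized or dosed | yes | no |
| Sensor already in place, randomized, dosed | no | yes |

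Row 2 loses both events and denominator. Row 3 adds denominator without procedural risk.

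**2. Inputs from the document**
- Target of 10 per dose at three doses: 3 × 10 = 30 randomized.
- Device- or system-related complication rates cited in heart failure: 8 of 575 in the pivotal trial (8/575 = 1.39%, agreeing with the 1.4% given), 1% in a second large trial, and 0.4% in a post-approval study.
- The article describes 550 patients as implanted and randomized in the pivotal trial. The complication denominator of 575 exceeds that by 25, so that benchmark is not restricted to randomized patients. A dosed-only rate from this trial would not be built on the same basis.

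**3. How few events to expect**

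Expected number = 30 × rate. Chance of at least one = 1 − (1 − rate)^30.
- 0.4%: 0.12 expected, chance 11%.
- 1%: 0.30 expected, chance 26%.
- 1.4%: 0.42 expected, chance 34%.

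At these rates the likely count is zero or one, so a single omitted event changes the reported figure noticeably. The rates come from heart failure, and the article itself notes that this population differs from PAH.

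**4. Illustration of the omission (assumed counts)**

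Let all 30 randomized be dosed, with e events among them. Let k more be implanted but not dosed, with m events. The stated set gives e/30; an all-implanted set gives (e + m)/(30 + k). The article gives neither k nor m. Intervals are exact (Clopper-Pearson) 95%.

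| k | e | m | Stated set | All implanted |
|---|---|---|---|---|
| 2 | 0 | 1 | 0/30 = 0% (0 to 11.6) | 1/32 = 3.1% (0.1 to 16.2) |
| 2 | 1 | 1 | 1/30 = 3.3% (0.1 to 17.2) | 2/32 = 6.3% (0.8 to 20.8) |
| 2 | 1 | 0 | 1/30 = 3.3% (0.1 to 17.2) | 1/32 = 3.1% (0.1 to 16.2) |
| 5 | 0 | 1 | 0/30 = 0% (0 to 11.6) | 1/35 = 2.9% (0.1 to 14.9) |
| 5 | 1 | 1 | 1/30 = 3.3% (0.1 to 17.2) | 2/35 = 5.7% (0.7 to 19.2) |
| 5 | 1 | 0 | 1/30 = 3.3% (0.1 to 17.2) | 1/35 = 2.9% (0.1 to 14.9) |

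One omitted event moves the estimate by about 2 to 3 percentage points. With no omitted event, the shift is under half a point in the other direction. The intervals are wide and overlap throughout.

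**5. Illustration of the previously implanted (assumed counts)**

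If 3 of the 30 dosed participants arrived with a sensor, one procedure event should be set against 30 − 3 = 27: 1/27 = 3.7%, not 1/30 = 3.3%. This effect is smaller than that of an omitted event, and it also pushes the rate down.

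**The case against.** The strongest reply is that the article never says which population is used for device events. It assigns the PK set to the PK analyses but gives the Safety Analysis Set no such assignment, and it names intention-to-treat and per-protocol approaches without defining them. The full protocol or SAP may contain an implanted set. This stands as a limit on certainty. It does not remove the mismatch: these are safety outcomes, only one safety population is stated, and that population cannot cover a stated part of the primary endpoint. If an implanted set exists, the sponsor need only say so.

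A second reply is that the trial's main purpose is the safety of three CS1 doses, for which a randomized-and-dosed set is suitable. That is correct, and it is why the point is moderate.

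A reader might also infer more than the text supports:
- **That every event before the first dose is lost.** The definition is a rule about who belongs, not a time window. An implant event in someone later dosed is not excluded.
- **That implant events would be shown only split by dose.** An overall summary is already planned.
- **That previously implanted participants do not belong in device safety at all.** They are at risk of operation and malfunction effects; only procedure-event denominators should leave them out.
- **That lost events would decide a device conclusion.** The article states no device hypothesis or threshold.

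**Conclusion.** The point holds as a mismatch between a stated endpoint component and the only stated safety population. It is confined to participants in whom implantation is attempted or completed and who are never randomized or dosed, plus a lesser dilution from participants with a sensor already in place. The expected direction is an understated procedure-related rate. That rests on the reasoning that a serious implant complication makes randomization less likely, and on the inference that device events are analysed on the Safety Analysis Set.

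A large bias might be inferred, but the document does not show one, because the number implanted but not dosed and the events among them are not given. Under the assumed counts, one omitted event takes 0% to about 3%, or 3.3% to about 6%. With no event among the undosed, the rate barely moves, and slightly the other way. The assessment of CS1 itself is not affected. Severity is moderate.

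**What to change.** Define a Device Safety Set of all consented participants with an attempted or completed in-study CardioMEMS implantation, whether or not they are later randomized. Count device and procedure events on it from the start of the procedure.

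- For events before randomization, use the pooled (overall) summary and do not attribute them to a dose.
- Leave previously implanted participants out of procedure-event denominators only. Keep them for operation and malfunction events, and show their number separately.
- Keep the randomized-and-dosed Safety Analysis Set for CS1 safety.
- State in the analysis plan which set serves each component of the primary endpoint. If the unpublished SAP already has such a set, confirming this is enough.

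The cost is one extra analysis set and one table. The participants concerned have already consented and undergone the procedure, and the design, randomization and sample size do not change. It should be settled before the results are analysed, because the rate depends on the denominator chosen.
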